### Data collection, management and analysis

Data will be collected in the participants’ homes on a paper case report form (CRF) and will subsequently be entered onto a secure password-protected electronic database. Outcome data will be entered by the research assistant who collected the data (and thus will be entered blind to treatment allocation). Each participant will be assigned a trial identity code number, allocated at randomization, for use on CRFs, other trial documents and the electronic database. The documents and database will also use their initials and date of birth.

CRFs will be treated as confidential documents and held securely in accordance with regulations. The investigator will make a separate confidential record of the participant’s name, date of birth, local social care number and participant trial number to permit identification of all participants enrolled in the trial, in accordance with regulatory requirements, and for follow-up assessments as required. Access to CRFs shall be restricted to those personnel approved by the chief investigator.

When data collection is complete, a data quality check will be conducted in duplicate by two researchers and a 10% sample of the database will be checked against the original paper CRF. Steps will be taken to minimize missing data via personal contacts throughout the study period from the investigator, and every attempt will be made to locate participants for follow-up assessment. Outcome data will be collected in person by a research assistant to minimize the amount of missing data. For each outcome measure used where data is missing, an imputed average will be used for items where less than 10% of the overall measure is missing. Where more than 10% of a measure is missing, the entire measure will be coded as missing.

The main endpoint for the study is determination of the feasibility of conducting a larger, powered study. Descriptive statistics will be used for this analysis, based on analysis of the trial screening and recruitment log, loss to follow-up and analysis of the acceptability questionnaire. Analysis of outcome data will be by the intention-to-treat principle, and participants will be analyzed according to their treatment assignment irrespective of whether they completed the treatment. It will not be possible to collect any outcome data for those who discontinue participation in the study. The data collected from the outcome measures in the trial will be presented using summary statistics, and any differences between the arms will be calculated at two-week, three-month and six-month follow-up assessments, along with the 95% confidence intervals. This data will be used to inform a sample size calculation, treatment effect estimate and to determine the appropriateness of these measures for use in a larger, powered study. Assistance from a statistician will be available as required. A health economist will provide input for the economic evaluation of the intervention and analysis of the EQ-5D data.

A Trial Steering Committee (TSC) is in place and includes experienced health and social care researchers, social care staff, an experienced geriatrician and public and patient representatives. Ethical approval for this study was provided by The Social Care Research Ethics Committee (approval number: 13/IEC08/002), and management approval has been obtained from the trial site.

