### Outcomes

The primary trial outcome will be a determination of the feasibility of conducting a larger, appropriately powered trial. The assessment of feasibility will be a composite measure of recruitment, retention, acceptability and the viability of delivering the intervention. Key aspects to be addressed are: whether the eligibility criteria are realistic, whether service users are willing to be randomized, the dropout rate, the content and scheduling of the occupational therapy treatment visits, the acceptability of the occupational therapy intervention, the most suitable primary outcome measure for the main study and the feasibility of the cost data collection.

The participant outcomes to be assessed will be: personal and extended ADL, health and social care-related quality of life, number of care support hours, health and social care service usage and carer strain. The measures are: Barthel Index (BI), Nottingham Extended Activities of Daily Living (NEADL), Short-Form 36 (SF-36), Adult Social Care Outcomes Toolkit (ASCOT), EQ-5D and Caregiver Strain Index (CSI). Additionally, information will be collected on: number of homecare hours, falls, admissions (to acute and residential services) and use of health and community services. The Mini-Mental State Examination will be completed at the baseline time point in order to provide a description of the sample. The timeline and proposed flow of participants through the study are shown in Figure 1.

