### Sample size and recruitment strategy

For a feasibility study, no formal sample size calculation is required. The aim is to recruit 50 participants (25 in each arm of the trial) to test the randomization process and the acceptability of the intervention. The trial will recruit for eight months. Current data from the trial site suggests that approximately three service users per week will be eligible. A maximum of 10 participants will be recruited per calendar month. Potential participants will be approached in the order in which they are referred to the re-ablement service. If 10 participants consent during a calendar month, recruitment will cease until the first new referral of the next calendar month. If the maximum of 50 participants are recruited before the end of the eight-month period, recruitment will cease.

Participants will be enrolled into the study by the investigator. The process for obtaining informed consent will be in accordance with the Research Ethics Committee (REC) guidance, and Good Clinical Practice (GCP) and any other regulatory requirements that might be introduced. The investigator and the participant shall both sign and date the informed consent form before the person can participate in the study. Randomization will be generated online by the Nottingham Clinical Trials Unit (NCTU) using a web-based randomization program. Participants will be individually randomized in random varying block sizes (sized in order to deliver the clinical intervention appropriately). Randomization will be at a ratio of 1:1 (treatment-to-control). Only the NCTU will have access to the allocation sequence. Baseline assessments will be completed prior to randomization. Follow-up assessment visits will be completed by a research assistant who is masked to the treatment allocation. It is possible that participants may reveal their treatment allocation to this assessor, and any instances of this will be recorded as part of the assessment of feasibility.

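### The missing-item rule gives no outcome at exactly 10% missing and is applied to the whole instrument, so some incomplete forms have no defined score and completed parts of an instrument can be discarded (minor)

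*Protocol article*

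**What the plan says.** The rule is in the Protocol article under Data collection, management and analysis. Its scope is general: "For each outcome measure used where data is missing". It has two branches. In the first, "an imputed average will be used for items where less than 10% of the overall measure is missing". In the second, "Where more than 10% of a measure is missing, the entire measure will be coded as missing".

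The Outcomes section shows what counts as a measure. It lists whole instruments: "The measures are: Barthel Index (BI), Nottingham Extended Activities of Daily Living (NEADL), Short-Form 36 (SF-36", followed by ASCOT, EQ-5D and the Caregiver Strain Index. It names no subscales and gives no item counts, apart from the number in the name SF-36. The article gives no instrument-specific scoring rule.

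The scores are to be summarised by arm at each follow-up, with differences and 95% confidence intervals. They will inform a sample size calculation and a treatment effect estimate, and help "determine the appropriateness of these measures for use in a larger, powered study". On size, Sample size and recruitment strategy states: "The aim is to recruit 50 participants (25 in each arm of the trial").

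**The concern.** There are two faults in the rule as written.

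- **Boundary.** One branch needs strictly less than 10% missing and the other strictly more. A form with exactly 10% missing meets neither condition. Whoever scores it must choose between imputing and deleting, possibly after seeing the data.
- **Unit.** The percentage is taken over the whole instrument, and so is the deletion. If an instrument yields several separately scored scales, blanks in one scale can remove others that were fully answered. Conversely, blanks that all fall in one scale can be imputed because they are few relative to the whole instrument.

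What is at stake is the set of usable scores behind the between-arm differences, the variance estimates for the next trial's sample size, and the judgement on which measure suits that trial. With 25 per arm, a handful of scores lost or settled ad hoc is noticeable.

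**Working it through.** The article gives no derived figure to reproduce. The check applies the two written conditions to m blank items out of k, using the exact fraction m/k.

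**Inputs from the article:** impute if m/k < 10%; delete the whole measure if m/k > 10%; 50 participants; 36 items for the SF-36, from its name.

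**Assumptions, not in the article:** 10 items for the Barthel Index (range 8–15 shown); 20–22 items for the NEADL; the SF-36 has separately scored scales; the item-blank rates used below.

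**Step 1: where the gap can occur.** m/k = 1/10 requires k = 10m, so exactly 10% arises only when the item count is a multiple of 10.

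**Step 2: the rule applied.**

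| Instrument | Blanks | Share | Outcome under the rule |
|---|---|---|---|
| Barthel, 10 items (assumed) | 1 | 1/10 = 10.0% | none defined |
| Barthel, 10 items (assumed) | 2 | 2/10 = 20.0% | deleted |
| Barthel, if 8 or 9 items | 1 | 12.5% or 11.1% | deleted |
| Barthel, if 11 to 15 items | 1 | 9.1% to 6.7% | imputed |
| NEADL, if 20 items | 2 | 2/20 = 10.0% | none defined |
| NEADL, if 21 or 22 items | 2 | 9.5% or 9.1% | imputed |
| SF-36, 36 items | 3 | 3/36 = 8.3% | imputed |
| SF-36, 36 items | 4 | 4/36 = 11.1% | whole SF-36 deleted |

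For a 10-item form the smallest non-zero share is 10.0%, so the imputation branch is never reached: one blank is undefined and two or more are deleted. The SF-36 result does not depend on whether 35 or 36 items are counted (3/35 = 8.6%, 4/35 = 11.4%).

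**Step 3: how often, for illustration.** Let each item be blank independently with probability p.

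- Exactly one blank of 10: 10 × p × (1 − p)^9.
- Four or more blanks of 36: 1 − Σ C(36, j) p^j (1 − p)^(36 − j), for j = 0 to 3.

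| p | Exactly 1 of 10 | Per 50 forms | 4 or more of 36 | Per 50 forms |
|---|---|---|---|---|
| 0.2% | 2.0% | 1.0 | negligible | 0 |
| 1% | 9.1% | 4.6 | 0.05% | 0.03 |
| 2% | 16.7% | 8.3 | 0.6% | 0.3 |
| 3% | 22.8% | 11.4 | 2.2% | 1.1 |

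For example, at p = 1%: 10 × 0.01 × 0.99^9 = 0.1 × 0.9135 = 0.091.

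Independence matters. If blanks cluster, for instance through a skipped page, loss of the whole SF-36 becomes more frequent than shown and isolated single blanks tend to become less frequent.

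**The case against.** The case for leaving this alone is mainly about weight, and much of it stands.

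- **The item count is not in the article.** A reader might infer that one blank Barthel item is certainly unscored. That holds only for a 10-item version; with 8–9 or 11–15 items a single blank has a defined outcome. The boundary gap itself does not depend on this.
- **No blank rate is given, and the design points to a low one.** A research assistant collects the outcome data face to face, expressly to limit missing data. At 0.2% per item, only about 1 form in 50 would fall in the gap. The upper end of the range is an illustration, not a forecast.
- **Losing the whole SF-36 is rare under random blanks.** A reader might infer heavy losses, but at 1–3% the expected number is about one form or fewer per 50. The point rests on clustered blanks and on the unit being poorly chosen.
- **Short instruments.** A reader might count EQ-5D or ASCOT forms lost through a single blank. Coding a short form as missing is a defined outcome, however, and the change proposed here would not recover a five-item form with one blank under its 10% fallback. Those losses are not part of this point.
- **Choice of measure.** A reader might infer that completion after coding will decide the next trial's primary outcome. The article says only that the outcome data inform appropriateness, and raw blanks can still be counted from the case report forms.
- **Whose average is imputed** is unstated, but that detail is commonly left to an analysis plan and is not held against the article.

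One objection fails: that the whole matter is detail for an analysis plan. The article states an operative rule with a fixed threshold and a fixed unit, and following it as written produces the results above.

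**Conclusion.** The point holds as a minor defect in a stated rule. Two facts follow from the text alone: exactly 10% missing has no outcome, and both the threshold and the deletion apply to the whole instrument. Four blanks of 36 therefore remove the entire SF-36, while three are imputed wherever they fall.

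Two consequences rest on assumptions: that a single Barthel blank is undefined (10 items), and that completed SF-36 scales are discarded (separately scored scales). The likely size is small: roughly 2–23% of 10-item forms with exactly one blank at 0.2–3% item missingness, with the lower end more plausible given in-person collection, and about 0.05–2% of SF-36 forms deleted at 1–3%, more under clustering.

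A reader might infer that the feasibility conclusion is at risk. The documents do not support that: the main endpoint is assessed descriptively from the screening and recruitment log, loss to follow-up and the acceptability questionnaire, none of which passes through this rule. What it touches are the secondary summaries and the planning inputs for the next trial.

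**What to change.** Replace the two sentences of the rule with:

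> Where an instrument has its own scoring rule for missing items, that rule is applied to each separately scored scale. Otherwise, if 10% or fewer of a scale's items are missing, the participant's own mean of the remaining items in that scale is used; if more than 10%, that scale (not the whole instrument) is coded as missing.

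Add that raw item completeness will be reported for each measure before any imputation, so that differences between instruments are not partly created by the rule.

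This closes the boundary, confines any loss to the affected scale and settles which average is meant. Under the fallback, a scale with fewer than 10 items is still coded missing after one blank (for example 1/9 = 11.1%), but that is now an explicit outcome.

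The cost is a few sentences of wording and one descriptive table, with no change to data collection or sample size. It should be settled before outcome data are examined by arm.

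### Arm differences at each follow-up are described without use of the pre-randomization assessments: valid on a plain reading, but less precise than the data allow with 25 per arm

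*Protocol article*

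**What the plan says.** The analysis is set out in the protocol article under Data collection, management and analysis. Outcome measures are to be presented with summary statistics, after which "any differences between the arms will be calculated at two-week, three-month and six-month follow-up assessments, along with the 95% confidence intervals". No model and no covariate is mentioned. The same paragraph gives these results a purpose: they are to feed the sample size and the effect estimate of the larger trial and to help judge which measures suit it. On dropout it says: "It will not be possible to collect any outcome data for those who discontinue participation in the study".

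Under Sample size and recruitment strategy, the article states: "Baseline assessments will be completed prior to randomization". Allocation is 1:1, and "Participants will be individually randomized in random varying block sizes". No stratification on baseline function is mentioned. The size is 25 per arm, with the remark that "For a feasibility study, no formal sample size calculation is required".

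Under Outcomes, the scales are the Barthel Index, NEADL, SF-36, ASCOT, EQ-5D and Caregiver Strain Index. Homecare hours, falls, admissions and service use are collected as well. The only instrument that the text places explicitly at baseline is the Mini-Mental State Examination, to describe the sample. The timeline figure, which may list the others, is not available here.

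**The concern.** Calculating a difference from summary statistics at each visit uses the follow-up scores alone. With 25 per arm and no stratification on function, the arms can differ noticeably at baseline by chance. An unadjusted difference then carries part of that imbalance with it. Where a scale was also measured before randomization, conditioning on that score removes this component and usually shortens the interval.

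The stakes are in planning. A later trial that adjusts for baseline needs the residual SD, or the raw SD together with the baseline/follow-up correlation. The analysis as described commits to reporting neither the residual SD nor the correlation. A sample size built on the raw SD alone would be larger than an adjusted analysis needs.

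There is also a smaller point on dropout. When visits are analyzed separately, a participant seen at two weeks but lost by six months adds nothing to the six-month estimate. A model across visits would use the earlier score.

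**Working it through.** **Plan's own figure.** 25 + 25 = 50, as stated. No SD, effect size, power or dropout rate is given, so there is nothing further to reproduce.

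**Inputs.** From the article: n = 25 per arm, 1:1 allocation and 95% intervals. Assumed: the correlation r between baseline and follow-up, shown from 0 to 0.8, because the documents give none. All results are in SD units of the scale.

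**Chance imbalance at baseline.** The SD of the difference in baseline means is √(2/25) = 0.283.
- P(|imbalance| > 0.3 SD) = 2[1 − Φ(0.3/0.283)] = 0.289, or 29%.
- P(|imbalance| > 0.5 SD) = 2[1 − Φ(0.5/0.283)] = 0.077, or 7.7%.

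Given an imbalance d, the unadjusted difference is expected to shift by r × d. For d = 0.5 this is 0.15, 0.25 and 0.35 SD at r = 0.3, 0.5 and 0.7.

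**Interval half-width.**
- Unadjusted: t(0.975, 48) × √(2/25) = 2.011 × 0.283 = 0.569.
- Adjusted for baseline (ANCOVA, expected): t(0.975, 47) × √[(2/25)(1 − r²)(1 + 1/46)] = 0.575 × √(1 − r²).

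| r (assumed) | Adjusted half-width | Change from 0.569 |
|---|---|---|
| 0 | 0.575 | 1% wider |
| 0.2 | 0.564 | 1% narrower |
| 0.3 | 0.549 | 4% narrower |
| 0.5 | 0.498 | 12% narrower |
| 0.7 | 0.411 | 28% narrower |
| 0.8 | 0.345 | 39% narrower |

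With 20 per arm analyzed (an assumed loss), the unadjusted half-width is 0.640. The adjusted values are 0.620, 0.563 and 0.464 at r = 0.3, 0.5 and 0.7, so the relative gain is nearly the same.

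**Validity.** In 10,000 simulated trials of 25 per arm at each r, coverage of the unadjusted interval was 94.8%, 94.5% and 95.0% at r = 0.3, 0.5 and 0.7. The adjusted interval covered 94.9%, 94.8% and 94.9%. Both hold their nominal level, and they differ only in width.

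**Planning.** If the larger trial adjusts for baseline but is sized on the raw SD alone, its sample size is too large by about 1/(1 − r²). That factor is 1/0.75 = 1.33 at r = 0.5, 1/0.51 = 1.96 at r = 0.7 and 1/0.36 = 2.78 at r = 0.8.

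**The case against.** The strongest reply is that the article nowhere calls the differences raw or unadjusted. An adjusted mean difference at each visit would also fit the wording, and a condensed article often leaves the model to a fuller document. This stands in part: that the analysis is unadjusted is an inference. It is still the plain reading of a sentence that goes from summary statistics to differences between arms and names no covariate.

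Several stronger readings are tempting, and the documents do not support them.
- *The intervals are wrong, or the estimates biased.* Over randomization the unadjusted difference is unbiased, and its interval already allows for chance imbalance. The 29% describes variability that the interval covers.
- *Every outcome can be adjusted.* No baseline value is stated for falls, admissions, homecare hours or service use. Apart from the Mini-Mental State Examination, the text does not list the baseline instruments.
- *Early data are discarded for those who leave.* A two-week score still enters the two-week comparison. It is only not used for later visits.
- *The gain is certain to be large.* Widths 20% to 40% narrower need r of about 0.6 to 0.8. Users recovering from illness or injury, followed to six months after discharge from the service, could well show lower correlations.

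It is also fair to say that the raw SD is a legitimate planning input, and that the correlation can be computed later wherever baseline scores exist. Nothing is lost for good. What remains is that the plan does not commit to reporting it.

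**Conclusion.** The point holds as a modest improvement in efficiency and reporting. On its plain reading the plan describes a valid analysis that leaves precision unused. The size depends on a correlation that the documents do not supply: a cost of about 1% in width at zero, a small gain at 0.3, and a substantial one from 0.5 upward. It also assumes that at least some of the scales are among the pre-randomization assessments.

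No primary conclusion is at risk. The main endpoint is feasibility, handled descriptively, and the article states no test or power claim for these outcomes. The point matters because the arm differences are meant to inform the design of the larger trial.

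**What to change.** In the analysis paragraph, state that for each scale measured at baseline the arm difference at each of the three visits will be adjusted for the baseline score and reported with its 95% interval. Either ANCOVA at each visit or one repeated-measures model (baseline score, arm, visit as a category, arm-by-visit) will do. The second uses every available visit, including those of participants who later leave.

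Report the raw SD, the residual SD and the baseline/follow-up correlation for each such scale, so that the larger trial can be sized for the analysis it will use. Keep raw means by arm as descriptive tables. Leave falls, admissions, homecare hours and service use as described.

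The cost is a change of wording and slightly more analysis work, with about 1% of precision lost if the correlation is near zero. No new data are needed for scales already assessed before randomization.

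### The protocol lets arm differences from 25 or fewer people per arm inform the main trial's treatment effect and sample size, and names no target difference from outside the study

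*Protocol article*

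**What the plan says.** Under Sample size and recruitment strategy, the protocol article states "For a feasibility study, no formal sample size calculation is required" and gives the purpose of the chosen number: "The aim is to recruit 50 participants (25 in each arm of the trial) to test the randomization process and the acceptability of the intervention". Precision for an efficacy outcome is not among the reasons given.

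Under Data collection, management and analysis, outcome data are to be shown as summary statistics, and "any differences between the arms will be calculated at two-week, three-month and six-month follow-up assessments, along with the 95% confidence intervals". The next sentence gives the use: "This data will be used to inform a sample size calculation, treatment effect estimate and to determine the appropriateness of these measures" in a larger, powered study. The same section warns about losses: "It will not be possible to collect any outcome data for those who discontinue participation in the study". No expected loss rate is given, since dropout is one of the things the study is meant to learn.

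Under Outcomes, one of the feasibility questions is "the most suitable primary outcome measure for the main study and the feasibility of the cost data collection". Six instruments are listed there, together with care hours, falls, admissions and service use.

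The article states no minimum important difference or other external target effect, and no SD, significance level or power for the main trial.

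**The concern.** A sample size calculation for two means needs a variability and a target difference. This study can help with the first. For the second, the only source the article names is the study's own outcome data, and the only part of those data that yields a treatment effect is the observed difference between arms. The study was not sized to estimate that difference.

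This matters because required sample size varies with the inverse square of the effect, so a modest error in the effect becomes a very large error in the sample size. An estimate that is too large by chance leads to an underpowered main trial. One that is too small leads to a trial far larger than needed, and one at or below zero gives no usable sample size. Laying the foundations for a powered study is this study's declared purpose, so the sentence bears on its main product.

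**Working it through.** **Inputs from the protocol article.** 50 participants, 25 per arm, 1:1 allocation (Sample size and recruitment strategy); 95% confidence intervals for arm differences (Data collection, management and analysis). The figure of 50 comes from no formula, so there is no calculation to reproduce; 2 × 25 = 50 agrees with the allocation ratio.

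**Assumptions, because the article gives no figures.** Outcomes standardised to SD = 1; loss of 0% or 20% (25 or 20 analysed per arm); true effect 0.3 or 0.5 SD; main trial at two-sided 5% with 90% power.

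**Step 1: precision of the arm difference.** SE = √(2/n); half-width = t(0.975, 2n − 2) × SE.
- n = 25: SE = √(2/25) = 0.283; half-width = 2.011 × 0.283 = 0.57 SD.
- n = 20: SE = √(2/20) = 0.316; half-width = 2.024 × 0.316 = 0.64 SD.

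**Step 2: main-trial size at the true effect.** n per arm = 2(1.960 + 1.2816)²/d² = 21.01/d². At d = 0.3 this is 233.5, or about 233 per arm (234 rounded up).

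**Step 3: main-trial size at the observed effect, when the true effect is 0.3.** Quartiles of the observed effect = 0.3 ± 0.6745 × SE.

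| Analysed per arm | Middle half of observed effects | Implied n per arm | Chance that observed effect ≤ 0 |
|---|---|---|---|
| 20 | 0.087 to 0.513 | 21.01/0.087² ≈ 2,800 down to 21.01/0.513² ≈ 80 | Φ(−0.3/0.316) = 17% |
| 25 | 0.109 to 0.491 | about 1,760 down to 87 | Φ(−0.3/0.283) = 14% |

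The table uses unrounded quartiles. Half of all results would fall outside these ranges.

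**Step 4: real power of a trial sized on the observed effect.** At 80% power the constant is 2(1.960 + 0.8416)² = 15.70. A trial sized for 90% power on the observed effect therefore has true power below 80% when the observed effect exceeds √(21.01/15.70) = 1.157 times the true one. For a true effect of 0.3 the threshold is 0.347.
- 20 per arm: P(observed > 0.347) = 0.441 and P(observed > 0) = 0.829, so given a positive estimate the chance is 0.441/0.829 = 53%.
- 25 per arm: 0.434/0.856 = 51%, so the result hardly depends on the assumed loss.
- True effect 0.5 with 20 per arm: 0.402/0.943 = 43%.

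**Step 5: taking only the SD from this study.** With the target difference fixed from outside, n is proportional to the variance. The 95% chi-square interval for the variance, relative to its estimate, is 0.67 to 1.66 on 38 df (20 per arm) and 0.70 to 1.56 on 48 df (25 per arm). The uncertainty in n over a 95% interval is thus about 1.66/0.67 = 2.5-fold. The observed effect gives about 2,800/80 = 35-fold over the middle half alone.

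**The case against.** The strongest reply is that the sentence is soft and broad. It says the data will inform the calculation, not fix it. The data referred to include summary statistics, and taking SDs, completion and retention from a feasibility study into a sample size calculation is sound practice. The differences will carry 95% intervals that display the imprecision, no hypothesis test is planned, and feasibility is the main endpoint. The harm arises only if a later team uses the point estimate and ignores both its interval and any important difference. It concerns a future trial, not the conduct or data of this one.

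Most of this stands and limits the point. It does not remove it: a treatment effect estimate is named as a product in its own right, summary statistics such as SDs and retention cannot supply one, and no other target is offered. A confidence interval shows the imprecision but does not stop the point estimate being used.

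A reader might go further and infer that the main trial's primary outcome will be whichever measure shows the largest arm difference, and might then count the chance findings among six instruments at three visits. The article does not support that. It says the data will bear on whether the measures are appropriate, and it lists the choice of primary outcome among recruitment, dropout, acceptability and cost-data questions. Judging measures on completeness or variability fits that wording equally well. A missing selection rule may also simply sit in the full protocol. Nor does any stop-or-go rule depend on the arm difference, so the article gives no basis for saying that the main trial would be wrongly abandoned because of it.

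**Conclusion.** The point holds in a limited form. The article names data that include the observed arm differences as a source for the main trial's treatment effect and sample size, from a study of 25 or fewer per arm not sized for efficacy, with no external target difference. An estimate with a 95% half-width of 0.57 to 0.64 SD cannot serve as that effect size. If the true effect is 0.3 SD, a main trial sized on it would have under 80% real power about half the time when the estimate is positive, and the estimate would be zero or reversed 14% to 17% of the time.

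The half-widths rest only on the number analysed, with the 20% loss behind the upper one assumed. The other figures also rest on the assumed true effect and power, which the article does not give. The use of SDs, completion and retention is not in question. This is a recommended change of wording, not a defect that must be cured before the study can run.

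**What to change.** Reword the sentence in Data collection, management and analysis to say four things:

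1. The main trial will be powered on a pre-specified important difference, justified from outside this study.
2. This study will supply the SD of the candidate outcomes with its confidence interval, and the completion, retention and uptake rates.
3. Arm differences with 95% confidence intervals are descriptive and will not be used as the main trial's effect size.
4. The suitability of the measures, including the choice of primary outcome raised under Outcomes, will be judged on completeness, floor and ceiling effects, variability and burden, not on arm differences. The article does not say otherwise; stating it closes off the other reading.

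The cost is wording only: no participant, visit or procedure changes. The one real demand is that a target difference must be found and justified from elsewhere, for whichever measure is chosen.
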